**Fig. 1 Fig1:**
[figure not shown]
Map showing 60 candidate study clusters identified in Muheza District, including core (coloured) and buffer (*white*) areas

The study cohort of village children aged 6 months to 11 years old, who live in core cluster areas, will be enrolled to assess the effectiveness of the interventions on malaria parasitaemia (asymptomatic and symptomatic), the prevalence of anaemia and the costs associated with malaria infection and treatment. One hundred and ten children per cluster will be randomly selected and followed monthly for 1 year after intervention. No distinctions will be made regarding gender, ethnic group, medical condition or physical health. For households with multiple, eligible children, all potential participants will be recruited. Children will only be included in the cohort provided their parents/guardians give witnessed informed written consent or in the case of older children, personal assent is obtained. If consent is not provided then replacement children will be randomly selected from those remaining in the cluster. Assurance will be sought from parents/guardians that their child will remain resident in the village throughout the study year. Participants and households are free to withdraw from the study at any time with impunity.

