During the ITWL intervention period, all core and buffer households will be visited 6–10 days following installation to document any AEs. Adverse event monitoring will also occur among ITWL installers through a passive AE monitoring chain. Throughout the study year, AEs will be monitored actively in each monthly cohort follow-up visit, during which the clinical team will ask the parents of cohort participants to report all AEs for any members of their household. Cohort members will also be given a study card to take to local health facilities, which will be used to record any AEs arising between monthly study visits. Other study participants will report AEs at any point to the CHWs, health facility or study team through a passive AE monitoring chain in both core and buffer areas. All AEs such as skin or eye irritation, respiratory problems, dizziness, nausea etc., will be graded in terms of severity (mild, moderate or severe), seriousness (based on patient outcome) and relatedness to the intervention by comparison with the control arm [58]. Appropriate management for any AE will be provided according to local guidelines and the outcome of AEs, including resolution, persistent disability, birth defect or death will be recorded.

In the case of a serious adverse event (SAE), the study clinician will record and manage the SAE in accordance with Good Clinical Practice (GCP) and report these to the PI who will inform the responsible member of the trial DSMB. Excessive grouping of SAEs by village or cluster will be reported to the DSMB and respective institutional ethics committees. A determination by the DSMB that there is potential harm to participants or the environment caused by the interventions will result in discontinuation of the study.

If an individual or household wants to terminate their participation, no further follow-up will be performed. If a cohort participant misses three consecutive monthly follow-up visits, they will be excluded from the study analysis. There will be no participant replacement during the surveillance period. If a household withdraws that was participating in the durability monitoring, it will be substituted with a neighbouring house of similar construction, where possible; there will be no other household or village replacements.

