### Study endpoints

#### Epidemiological

Primary endpoint: the cumulative incidence of malaria parasitaemia (asymptomatic and symptomatic) defined as the number of mRDT-confirmed episodes of parasitaemia per child per year. A child will be considered to have experienced an episode of parasitaemia during a given month if they had a positive mRDT during the scheduled monthly follow-up visit, irrespective of symptoms. Two consecutive positive scheduled mRDT results will be treated as two separate episodes and any malaria cases diagnosed and treated at health facilities between monthly visits will also be counted as episodes.

Secondary endpoints: (i) time to first episode of malaria parasitaemia (asymptomatic and symptomatic) as determined by mRDT as per the primary case definition; (ii) changes in mean levels of haemoglobin among cohort children aged 6 to 59 months.

All study outcomes will be compared between the intervention (ITWL + LLINs) and the control arm (LLINs only).

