### Data analysis

All statistical analyses will be performed using STATA version 13 (StataCorp LP, College Station, TX, USA). The primary endpoint will be a comparison of the cumulative incidence of symptomatic or asymptomatic episodes of malaria in children between the two intervention groups. Data from cohort members who are lost to follow-up or who missed monthly visit(s) will be treated as censored. Similarly, children who are taking anti-malarial drugs, based on a positive mRDT, will be excluded in the analysis for the first 2 weeks following treatment. History of travel away from the study village will be recorded during monthly visits and time at risk will be censored for such periods. In addition, malaria cases in children who resided outside their cluster area for more than half of the elapsed study period at the time of illness will be excluded.

An initial analysis will compare the cumulative malaria incidence rates between the two study arms to assess the number of episodes of malaria parasitaemia (symptomatic, asymptomatic or combined) per child per year. A follow-up analysis will examine the time to first episode of clinical malaria. The rate ratio (RR) will be calculated by dividing the incidence rate in the intervention relative to the control arm. The effectiveness of ITWL + LLINs vs. LLINs alone will be obtained from the final analysis as 1-RR. Cox regression modeling will be used to investigate potential confounding such as season and age. A priori confounders will be included in the model and that the presence of effect modification or interaction terms will be explored. Both intention to treat (all persons randomized) and per protocol analyses (all persons who received the intervention) will be conducted. All analyses will be adjusted for within-cluster correlation using generalized estimating equations or random effects models with gamma frailty. In addition, missing data will be analyzed and multiple imputation used, if required.

Similarly, mean haemoglobin in 6–59 month olds will be measured and compared between the two arms.

Other outcome variables, including entomological indices, cost-effectiveness and acceptability of interventions will be compared between study arms accounting for any correlated observations within clusters or households.

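### Leaving out children who miss three visits in a row conflicts with the protocol's own censoring rule and its intention-to-treat definition, and makes the primary analysis set depend on attendance after randomisation

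*Protocol article*

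**What the plan says.** Two sections of the protocol article govern children with missed visits.

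- *Trial oversight, safety considerations and handling withdrawals/drop-outs*: "If a cohort participant misses three consecutive monthly follow-up visits, they will be excluded from the study analysis". The next sentence adds: "There will be no participant replacement during the surveillance period". Nothing limits the exclusion to a per-protocol or sensitivity analysis.
- *Data analysis*: "Data from cohort members who are lost to follow-up or who missed monthly visit(s) will be treated as censored". On travel away from the village, "time at risk will be censored for such periods". On analysis sets: "Both intention to treat (all persons randomized) and per protocol analyses (all persons who received the intervention) will be conducted". On missing data: "In addition, missing data will be analyzed and multiple imputation used, if required".

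The primary endpoint under *Study endpoints* is a rate, "defined as the number of mRDT-confirmed episodes of parasitaemia per child per year". It also counts malaria diagnosed and treated at health facilities between visits. *Study area and participant recruitment* says that 110 children per cluster "will be randomly selected and followed monthly for 1 year after intervention". *Sample size rationale* allows for 18 % loss to follow-up.

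**The concern.** The two sections give different instructions for the same child. One leaves the child out. The other keeps what was observed and stops counting where observation stops. An analysis that omits children because of later non-attendance is also not an analysis of everyone randomised.

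This bears on the primary comparison because attendance is determined after randomisation and installation cannot be blinded (*Randomization and blinding*). If families in one arm stop attending more often, or if those who stop differ in malaria risk by arm, omitting them changes the risk mix being compared. If the choice stays open until data are available, it could also be made with the results in view.

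**Working it through.** **1. The rules side by side.** Monthly visits run for 12 months.

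| Child | Exclusion rule, read literally | Censoring rule |
|---|---|---|
| Attends months 1–9, misses 10–12 | Nine observed months discarded | Nine months kept |
| Attends months 1–10, misses 11–12 | Kept (only two visits missed) | Ten months kept |
| Positive at month 2, misses 8–10, returns | Removed, although time to first episode is fully observed | Kept; the gap is censored |

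Other text presumes that such children stay in. *Randomization and blinding* says long absences will be taken into account in the analysis. *Data analysis* censors time away and, for children away more than half the elapsed period, excludes the malaria cases, not the child.

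**2. The plan's own figures.** 90 / (1 − 0.18) = 109.8, which reproduces the 110 children per cluster. For power I used the Hayes–Bennett formula for rates, with c = 22 clusters per arm, k = 0.302, control rate λ0 = 2.5, λ1 = 0.7 × 2.5 = 1.75, y = 90 child-years per cluster and two-sided 5 % (sidedness is assumed):

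- V = [(λ0 + λ1)/y + k²(λ0² + λ1²)] / (λ0 − λ1)² = [0.0472 + 0.8493] / 0.5625 = 1.594
- Power = Φ(√((c − 1)/V) − 1.96) = Φ(3.630 − 1.960) = 0.9525

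The stated power of more than 85 % is met as a lower bound.

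**3. Effect of the rule on power.** If the 18 % each contribute half a year (assumed), y rises from 90 to about 100. Power goes from 0.9525 to 0.9535 at λ0 = 2.5, and from 0.9541 to 0.9549 at λ0 = 3.0. This is negligible.

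**4. How many children.** 44 × 110 = 4,840, and 18 % of that is 871. If all 871 met the rule after 0.25, 0.5 or 0.75 year of observation, 218, 436 or 653 child-years would be discarded. At half a year, observed time is 4,840 × 0.82 + 436 = 4,404 child-years, so about 10 % goes. These figures are conditional: 18 % is total assumed loss, and the share meeting the three-visit rule is not stated.

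**5. Possible bias.** The protocol gives no loss by arm and no risk in those lost, so every scenario here is assumed. Let d be the fraction lost, r the rate in lost children relative to those who stay, and half a year the time observed before loss. With arm rate λ, the rate in those who stay is m = λ / (1 − d + d·r). Deletion compares m between arms. Censoring compares m·(1 − d + 0.5·d·r) / (1 − d + 0.5·d). True rate ratio 0.70:

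| Scenario | Deletion | Censoring |
|---|---|---|
| Same d and same r in both arms | 0.700 | 0.700 |
| d = 18 % in both; r = 1.5 control, 1.0 ITWL | 0.763 | 0.727 |
| d = 18 % in both; r = 1.0 control, 1.5 ITWL | 0.642 | 0.674 |
| d = 13 % control, 23 % ITWL; r = 1.5 in both | 0.669 | 0.688 |

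Second row worked: m is 2.5/1.09 = 2.294 in control and 1.75 in ITWL. Deletion gives 1.75/2.294 = 0.763. The censored control rate is 2.294 × 0.955/0.91 = 2.407, so censoring gives 1.75/2.407 = 0.727.

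With a true ratio of 1.0, the last three rows become 1.090, 0.917 and 0.955 under deletion, and 1.039, 0.963 and 0.983 under censoring.

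**6. Scale.** SE(log RR) ≈ √{[1/(90 × 2.5) + 1/(90 × 1.75) + 2 × 0.302²]/22} = √(0.1932/22) = 0.094. In the second row the two rules differ by ln(0.763/0.727) = 0.048, about half a standard error. Deletion itself is off by ln(0.763/0.70) = 0.086, about 0.9 of one.

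**The case against.** The strongest reply is that the exclusion sentence sits among drop-out procedures and never says that earlier data are erased. It may be a loose definition of drop-out, with *Data analysis* as the operative rule. On that reading the sections agree. This is possible, but what the sentence excludes is the participant, so deletion is the more literal reading. If the softer meaning was intended, the wording needs correcting all the same. A later analysis plan could choose between the rules, but both cannot be applied as written.

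A reader might go further and infer that the plan will remove several hundred children, or that it biases the result in a known direction. The documents support neither. The 18 % is not a count of children meeting the three-visit rule: those first lost in the last two months cannot meet it, and some who return after a gap can. Home visits and extended cluster visits are planned to limit missed visits. Differential loss and excess risk in lost children are assumptions. With a milder assumption the gap between rules is small. Suppose 30 % of children are mobile at twice the risk, 25 % of them are lost in control against 40 % in ITWL, and 13 % of the others are lost in both arms. Deletion then gives 0.677 and censoring 0.690, a gap of about 0.2 standard error.

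Nor are the discarded child-years a shortfall against plan, because the 90 children per cluster already give lost children no contribution.

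**Conclusion.** The conflict is established from the text and depends on no calculation: the exclusion sentence cannot be applied together with the censoring rule and the stated intention-to-treat set. Taken literally, it conditions the primary analysis on attendance after randomisation in an unblinded trial, so it exposes the rate ratio to attrition bias.

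How much bias would result is unknown. It is nil when loss and its link to risk are the same in both arms. In the assumed scenarios of the table it runs in either direction, from 0.642 to 0.763 around a true 0.70 under deletion, and from 0.674 to 0.727 under censoring. Censoring is therefore better but is no complete remedy for informative loss. The 871 children apply only if the whole assumed 18 % meets the rule. The exclusion brings no design benefit, because loss is already allowed for and a rate endpoint uses partial follow-up directly.

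**What to change.** Reconcile the two sections by removing the three-visit exclusion from the primary intention-to-treat analysis:

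- Keep every enrolled child's observed episodes and child-time, and censor only unobserved time.
- For a child who returns after a gap, apply one rule to numerator and denominator alike. Where the study booklet or health-facility record covers the gap, count both the documented facility episodes and the matching time. Otherwise censor both. A rule that counted only intervals with a completed visit could drop facility cases that *Study endpoints* counts as episodes and that the booklets recover at later visits (*Clinical evaluations and patient treatment*).
- If the three-visit set is kept, confine it to a labelled sensitivity analysis.
- Report by arm how many children met the three-visit rule.

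The cost is a short rewording of the protocol or analysis plan, settled before outcomes are compared by arm. It needs no extra data and no change to the sample size.

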### Intervention monitoring: ITWL

Prior to ITWL installation, quality control of the ITWL material will be assessed using WHO cone [55] and modified WHO cylinder bioassays [51] from a random sample of four rolls from each of five production lots (20 rolls total). From each ITWL roll, three 25 × 25 cm squares will be cut from a 2.5 × 1 m section for testing. Four WHO cone assays will be tested per ITWL sample for a total of 12 cone assays per roll. WHO cones will be fixed to the ITWL sample with frames and ten 2–5 day old unfed susceptible *An. gambiae* s. s. Kisumu mosquitoes or wild collected adult *An. gambiae* s. l will be exposed for 30 min; knockdown will be recorded after 1 h and mortality after 24, 48 and 72 h; the same experimental conditions will be used for WHO cylinder bioassays.

ITWL durability surveys will be conducted in 5 randomly selected households from eight intervention clusters (total of 40 households) at three, six and 12 months after intervention. At each follow-up, interviewers will survey the house to evaluate the condition of the ITWL installation and to record failed fixings, material tearing, causes of damage, proportion of walls still covered with ITWL and any evidence of ITWL repair, maintenance or attrition. In the same houses, ITWL in situ bioefficacy will be assessed using five WHO cone bioassays conducted as described above, at two wall heights (<1 m and >1 m from the floor) for a total of 10 bioassays per house. In addition, 5 × 5 cm samples of ITWL will be cut from house walls and insecticide content measured using HPLC according to the Collaborative International Pesticides Analytical Council (CIPAC) protocol.

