#### Entomological

Transmission parameters in the two study arms will be estimated from measurements made throughout the transmission season.

Primary endpoint: the EIR for *An. gambiae* s. l. and *An. funestus* s. l. estimated as the mean number of sporozoite infective bites/person/year.

Secondary endpoints: (i) the relative abundance of outdoor host-seeking *An. gambiae* s. l. and *An. funestus*; (ii) host feeding preferences of *An. gambiae* s. l.; (iii) changes in frequency (% mortality using diagnostic dose) and strength (LD_50_ and resistance ratio) of insecticide resistance to alphacypermethrin, permethrin, non-pyrethroid insecticides in each study arm; (iv) ITWL bioefficacy and durability over 12 months.

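### Replacing durability houses that withdraw can hide lining loss linked to withdrawal, so the 12-month physical-durability estimate may be overstated

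*Protocol article*

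**What the plan says.** Three parts of the protocol article bear on this point.

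- **Sample and measurements** (Intervention monitoring: ITWL). The survey covers "5 randomly selected households from eight intervention clusters (total of 40 households) at three, six and 12 months after intervention". Each visit records, among other items, "proportion of walls still covered with ITWL and any evidence of ITWL repair, maintenance or attrition". Cone bioassays are run on the installed lining of the same houses, and samples are cut from their walls to measure insecticide content.
- **Endpoint** (Study endpoints, Entomological). Secondary endpoint (iv) is "ITWL bioefficacy and durability over 12 months".
- **Withdrawal** (Trial oversight, safety considerations and handling withdrawals/drop-outs). The general rule is: "If an individual or household wants to terminate their participation, no further follow-up will be performed". For a durability household that withdraws, "it will be substituted with a neighbouring house of similar construction", if one can be found; this is the only replacement of a household or village that the section allows.

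Two further statements describe what a substitute would look like. Under Study intervention implementation, every core household of an intervention cluster is to be lined, and the study team neither repairs lining nor lines new houses once monitoring has started. A neighbour would therefore have been lined at the outset and left unrepaired since. The rule itself sets no condition on the state of the substitute's lining.

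**The concern.** For most endpoints a withdrawn unit is simply missing. Here the reason for leaving may be the outcome itself: a household that dislikes the lining, or has taken it down, has a plausible motive to leave the survey. Under the two rules together, that house is no longer observed and a participating neighbour fills its place. The count returns to 40, so the loss need not be visible in the denominator. The substitute is picked for proximity and similar construction, so the surveyed set is no longer the random sample that was drawn. A house that joins after a visit also has no survey record from that visit.

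The same section allows no replacement of cohort participants during surveillance and no other household or village replacement. The single exception falls on the endpoint where losing the unit may be the event of interest. The Discussion names durability in the field as one of the factors that decide operational success, and makes programme use conditional on it, so a flattering estimate would carry weight.

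**Working it through.** **Figures in the article.** 5 houses × 8 clusters = 40 houses, as stated. 5 cone assays × 2 wall heights = 10 per house, as stated. No power or precision is given for durability.

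**Inputs that the article does not give (assumed).**

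- w, the share of durability houses that withdraw: 5%, 10% or 20% (2, 4 or 8 of 40)
- s, lining loss in remaining houses, with substitutes taken to behave like them: 5% or 10%
- r, lining loss in withdrawn houses: from 0 to 100%

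**Formulas.**

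- Retention in the original 40 houses = 1 − [(1 − w)s + w·r]
- Retention reported with substitution = 1 − s
- Overstatement = reported − original = w(r − s)

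**Results at s = 10%, where substitution reports 90.0%.**

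| w | r | Original 40 | Overstatement |
|---|---|---|---|
| 5% | 50% | 88.0% | 2.0 points |
| 5% | 100% | 85.5% | 4.5 points |
| 10% | 50% | 86.0% | 4.0 points |
| 10% | 100% | 81.0% | 9.0 points |
| 20% | 50% | 82.0% | 8.0 points |
| 20% | 100% | 72.0% | 18.0 points |

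One row in full (w = 10%, r = 50%): 1 − (0.90 × 0.10 + 0.10 × 0.50) = 1 − 0.14 = 86.0%, and 90.0 − 86.0 = 4.0 points.

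At s = 5% and w = 10%, the overstatement is 0.10 × (0.50 − 0.05) = 4.5 points or 0.10 × (1.00 − 0.05) = 9.5 points.

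**Where it vanishes or reverses.** If r = s, the overstatement is 0. If r = 0 with w = 20% and s = 10%, it is 0.20 × (0 − 0.10) = −2 points, so durability is understated.

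**Scale.** The simple standard error of a 90% retention in 40 houses, ignoring clustering, is √(0.9 × 0.1/40) = 4.7 points.

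**What substitution itself contributes.** With 4 withdrawals and no replacement, the available houses give 36 × 0.90 / 36 = 90%, the same figure as with replacement. The expected bias therefore comes from not observing the withdrawn houses. Substitution adds the masking and the non-random selection.

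**Bioefficacy.** The corresponding shift is w(m − m_w), where m and m_w are mosquito mortality on lining in remaining and withdrawn houses. With assumed m = 80% and w = 20%, it is +4 points if m_w = 60%, −2 points if m_w = 90%, and 0 if the two are equal. Nothing in the article indicates which applies.

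**The case against.** The strongest reply has four parts.

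1. *The survey already counts lost lining.* A house that takes its lining down but stays in the survey is recorded as a loss through wall coverage and attrition. Removing lining is not the same as withdrawing. This stands: a reader might infer that lining loss disappears from the endpoint altogether, but only loss in houses that withdraw can be missed.
2. *The substitute need not be intact.* The rule asks for a similar neighbouring house and says nothing about its lining. Such a house carries lining that the study team has not repaired and may be damaged too. This also stands: the text does not support saying that a failed house is exchanged for a sound one, and the calculation above gives substitutes the same loss as the houses that remain.
3. *Substitution is not the cause.* Leaving withdrawn houses out gives the same expected figure. This is correct for the size of the bias. It does not excuse the rule, which restores the count to 40 without calling for withdrawn houses to be accounted for and brings in houses that were not randomly drawn.
4. *Withdrawal forms and the handling of substitutes belong in the full protocol or analysis plan.* This is fair as far as missing detail goes. The substitution and the end of follow-up are, however, fixed in the article, and following them as written can bias the endpoint.

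It can be added that with two withdrawals even the extreme case (4.5 points) is below the simple standard error of 4.7 points. That is true, but sampling error is reported with the estimate and this bias would not be.

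**Conclusion.** The point holds in a limited, conditional form. As written, the withdrawal rules leave lining loss uncounted in houses that withdraw because of the lining, and substitution masks this. Wall coverage and attrition may then look better than in the 40 houses sampled.

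The size depends on withdrawal and loss rates that the article does not give. For 5% to 20% withdrawal, with r from 50% to 100% and s of 10%, it runs from 2 to 18 points. The upper end needs every withdrawn house to have lost its lining. A reader might infer that the 12-month figure is bound to be overstated. The documents do not support that, because the direction depends on whether r exceeds s.

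Nor do they support extending the point to bioefficacy. Mortality is assayed on lining still in place, so its removal does not in itself raise the result. Overstatement there would need insecticidally poorer lining in the withdrawn houses, for which there is no evidence. The primary endpoint is not affected. A change is worthwhile because it is cheap and durability is meant to inform programme decisions.

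**What to change.** Amend the substitution rule along these lines:

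> Physical durability (wall coverage and attrition) is estimated in the 40 houses originally sampled. When a household withdraws, the reason and whether the lining is still in place are recorded. Lining already removed counts as attrition from that visit. Later status is treated as missing and reported with best- and worst-case bounds. Substitute houses serve only to maintain the number of cone bioassays and HPLC samples, and are reported separately.

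Recording status at the moment of withdrawal is compatible with stopping follow-up thereafter. Lining removed later stays unseen, and the bounds cover it. For example, with 4 of 40 houses of unknown status and 90% retention in the other 36, the worst case is 0.90 × 0.90 = 81% and the best case is 81% + 10% = 91%.

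The cost is a few sentences in the protocol and one added entry on the withdrawal form. The downside is slightly fewer observed houses for physical durability at 6 and 12 months, and possibly a less favourable figure.
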